### **7.5 Sensitivity Analyses for the Primary Outcomes**

A PP analysis is carried out as a sensitivity analysis compared with the results obtained using the FAS analysis. When the PPs and FAS analysis conclusions are not the same, it is necessary to analyze the possible reasons and discussion them.

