## 10. Sample Size Calculation

Estimates of clinically meaningful differences between the manual acupuncture group and the sham control group are based on the data of Nosyk et al. and our previous study [18,19,34]. We assume an efficacy rate of 70% for the manual acupuncture

group and 36% for the sham control group, 42 participants per group are needed at 5% significance with 90% power. This provided exceeding 99% power to detect a mean difference of 10 (SD 8) in opioid craving VAS scores between the two groups at a 5% significance level for a 2-sided test (required 25 participants per group). Thus, anticipating approximately 15% attrition, at least 50 participants per group (n = 100 in total) are required.

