## 11. Statistical Analysis

Statistical analysis will be performed by the Clinical Research and Big Data Laboratory, South China Research Center for Acupuncture and Moxibustion, Guangzhou University of Chinese Medicine. The statistician will be blinded to group allocation until final unblinding. SAS 9.4 will be utilized for data analysis. Missing data are filled by using multiple imputation.

Continuous variables are reported as the mean with standard deviation or median and interquartile range. Categorical variables are described as numbers and percentages using  $\chi^2$  test or Fisher's exact test. Longitudinal measures through 20 weeks (8 weeks of intervention and 12 weeks of follow-up) are analyzed for all outcomes. The analysis of proportion of participants with at least 20% reduction from baseline in the amount of methadone dose is performed using a generalized linear mixed-model. For opioid craving VAS and all secondary outcomes, analysis is conducted utilizing a linear mixed-model. For above models, values measured at baseline are used as covariates; intervention assignment, visit and intervention  $\times$  visit interaction are as fixed effects; and treatment centre and centre  $\times$  intervention interaction are as random effects. We assessed the poolability of treatment effects across centres by including centre  $\times$  intervention interaction in the model. If *P*-values corresponding to the centre  $\times$  intervention interaction term for both primary endpoints are greater than 0.10, the treatment effect is homogenous across centres [59].

Dynamic data will be demonstrated on the reduction in the methadone consumption and the opioid craving VAS score in the figures, separated by the manual acupuncture and sham group. Each row in the figures represents the reduction dose of

the daily consumption of methadone (the opioid craving VAS score) for one participant. Individuals who discontinue participation early appear at the bottom of each plot, whereas those with complete data appear at the top.

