To investigate the relationship between daily consumption of methadone and the intensity of opioid craving over a 20-week period, scatter plots are employed as a visual representation in this study with the x-axis representing the opioid craving VAS and the y-axis representing the daily consumption of methadone. The resulting scatter plot allows for the examination of the correlation between these two variables, providing insights into the potential influence of methadone intake on opioid craving levels over time.

Efficacy analyses will be performed for both the full analysis set (FAS) population and the per-protocol set (PPs) population. The FAS population will consist of all randomized patients who received at least one treatment. In a PPs analysis, only patients who complete all the clinical trials according to the protocol are counted towards the results. Besides, the PPs population in our research will meet these criteria: the experimental treatment requirements; the main variables can be determined; no missing baseline variables; no major violation of the test scheme. Safety analyses will be performed on the safety population, which will be comprised of all randomized subjects who have been administered at least one treatment. A PP analysis is carried out as a sensitivity analysis compared with the results obtained using the FAS analysis. When the PPs and FAS analysis conclusions are not the same, it is necessary to analyze the possible reasons and discuss them.

Primary outcomes used 2-sided tests at the 2.5% significance level. All other statistical tests are 2-sided at the 5% significance level.

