### **6.2 Study Populations**

All randomised patients who receive at least one session of acupuncture intervention and at least one efficacy measure will be included in the full analysis set. All randomised patients who completed all the intervention and 20 weeks follow-up assessments will be included in per-protocol analysis set.

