### **7.2 Missing Data**

We will use multiple imputation method under the missing at random (MAR) assumption for the primary and secondary outcome with missing data. Multiple imputations use the observed data to fill in the missing values repeatedly to give rise to multiple "pseudo-complete" datasets. We will perform the imputation of missing data 100 times using regression imputation, employing the SAS procedure Proc MI process. For each time point, measurements of primary and secondary outcomes are imputed using groups, baseline measurements, and measurements prior to the time point as covariates in regression models. The estimated values are set as integers, and 100 different datasets are generated. By calculating the median of all estimated values for missing data, the 100 imputed datasets are merged into one.

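### The only sensitivity analysis for the primary outcomes is per-protocol, which removes every dropout and so cannot show whether the dose-reduction result depends on missing at random

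*Combined protocol and SAP*

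**What the plan says.** On missing data, SAP 7.2 states: "We will use multiple imputation method under the missing at random (MAR) assumption for the primary and secondary outcome with missing data". The imputation model is given there too: "measurements of primary and secondary outcomes are imputed using groups, baseline measurements, and measurements prior to the time point as covariates in regression models". It has no shift parameter and no reference-based term. Section 11 of the protocol adds only this: "Missing data are filled by using multiple imputation".

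On sensitivity, SAP 7.5 and section 11 of the protocol give the same single analysis, per-protocol against FAS: "A PP analysis is carried out as a sensitivity analysis compared with the results obtained using the FAS analysis". If the two conclusions differ, the reasons are to be discussed. SAP 6.2 defines the comparison set: "All randomised patients who completed all the intervention and 20 weeks follow-up assessments will be included in per-protocol analysis set". The protocol's definition is also restricted to completers: "only patients who complete all the clinical trials according to the protocol are counted towards the results".

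Section 10 of the protocol sizes the trial "anticipating approximately 15% attrition". Each primary outcome is tested two-sided at 2.5% (SAP 7.4). Neither document plans a non-responder, delta-adjusted, tipping-point, reference-based or worst-case analysis. Early discontinuation otherwise appears only in the descriptive individual-patient plots of section 11 of the protocol.

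**The concern.** MAR cannot be verified from the observed data. The usual safeguard is to repeat the primary analysis under less favourable assumptions about the missing patients and see whether the conclusion survives. Per-protocol cannot do this. It deletes the patients in question, so its P-value does not move with their outcomes. It also changes other things at once: adherence, protocol violations, and the loss of patients who have week-8 data but leave before week 20.

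The documents give some reason to think that loss may be related to outcome. Protocol 4.2 and SAP 3.2.2 remove patients who take other medication for withdrawal, sleep, anxiety or depression during the study. A patient doing badly on a taper might well do so. If data collection stops at that point, and the documents do not say, missingness would follow poor outcome. At stake is whether a positive dose result could rest on responses credited to patients who were not observed, with nothing in the planned output to show it.

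**Working it through.** **The plan's own figure.** Protocol 10 uses 70% against 36%, two-sided 5%, 90% power. With unpooled variance, n = (1.960 + 1.282)² × (0.70×0.30 + 0.36×0.64) / 0.34², just over 40, so 41 per group. The pooled formula gives 44. The stated 42 lies between. Attrition: 42/0.85 = 49.4, so 50 per group. The figures reproduce.

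**Set-up.** 50 per arm, 42 observed and 8 missing. The 8 is an assumption taken from the planned attrition (50 − 42). The test is the uncorrected chi-square, that is z = (pA − pS) / √[p̄(1 − p̄)(1/nA + 1/nS)], as a stand-in for the planned mixed model. The threshold is 0.025. The missing-outcome scenarios are also assumptions.

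**At the planned rates.** The nearest whole numbers are 29/42 and 15/42. At those rates, 8 missing patients contribute about 6 responders (0.70×8 = 5.6) and 3 responders (0.36×8 = 2.9).

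| Handling of the 8 missing per arm | Acupuncture | Sham | z | P |
|---|---|---|---|---|
| Per-protocol (deleted) | 29/42 | 15/42 | 3.06 | 0.0022 |
| MAR-like FAS (observed arm rates) | 35/50 | 18/50 | 3.41 | 0.0007 |
| Non-response in both arms | 29/50 | 15/50 | 2.82 | 0.0048 |
| Both arms at the sham rate | 32/50 | 18/50 | 2.80 | 0.0051 |
| Acupuncture fails, sham at observed rate | 29/50 | 18/50 | 2.20 | 0.0275 |
| Extreme: acupuncture fails, sham all respond | 29/50 | 23/50 | 1.20 | 0.23 |

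For the fifth row: p̄ = 47/100, and z = 0.22 / √(0.47×0.53×2/50) = 0.22/0.0998 = 2.20. The per-protocol row is the same under every scenario, while the full-set P-value runs from 0.0007 to 0.23.

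**Range for the number missing.** In the fifth scenario with m missing per arm, acupuncture has about 0.70×(50 − m) responders and sham 0.36×50 = 18.

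- m = 4: 32 against 18, P=0.0051
- m = 6: 31 against 18, P=0.0093
- m = 7: 30 against 18, P=0.0163
- m = 8: 29 against 18, P=0.0275

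At the planned rates, significance is therefore lost only near the full planned attrition.

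**A smaller observed effect, 26/42 against 15/42.** Per-protocol gives P=0.0163. The MAR-like FAS (26+5 = 31/50 against 15+3 = 18/50) gives P=0.0093. The two agree, so SAP 7.5 would raise nothing. Non-response in both arms (26/50 against 15/50) gives P=0.0253, a borderline miss. The asymmetric case (26/50 against 18/50) gives P=0.107.

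**Across nearby results, sham held at 15/42.** With 26, 27, 28 or 29 acupuncture responders of 42, per-protocol (P=0.0163, 0.0088, 0.0045, 0.0022) and the MAR-like FAS (P=0.0093, 0.0051, 0.0027, 0.0007) both pass. The asymmetric case fails each time (P=0.107, 0.070, 0.045, 0.0275). At 30 it passes (P=0.0163).

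**Craving.** Shifting imputed acupuncture values by d mm moves the mean difference by (8/50)d = 0.16d. With SD 8, SE = 8×√(2/50) = 1.6, and the critical difference at 2.5% is 2.241×1.6 = 3.59. From the planned difference of 10, significance is lost at d = (10 − 3.59)/0.16, about 40 mm.

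**The case against.** Several counter-arguments have force.

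- A reader might infer that dropouts are ignored, or simply given their arm's response rate. The documents do not support this. The FAS imputes them, conditioning on baseline and earlier measurements, so a patient who worsened before leaving is imputed from that course. The 35/50 and 31/50 above are flat extrapolations. What remains is that the model still assumes no further difference between leavers and comparable stayers.
- A reader might infer that the planned comparison can never flag a problem. It sometimes would. At 25/42 against 15/42, the MAR-like FAS gives P=0.0163 and per-protocol P=0.0289, so the conclusions differ and a discussion of reasons is required. It would not isolate missingness as the cause.
- Under equal non-response in both arms the flip is narrow. With sham at 15/42 it occurs only at 25 and 26 acupuncture responders, and at 26 the miss is 0.0003 on a crude test. That margin proves little. The asymmetric scenario gives the stronger illustration.
- Fewer than 8 doses per arm may be missing. The protocol does not tie attrition to week 8. Methadone is taken daily at the clinic and dose records come from physicians (6.1.1), so a patient who stops acupuncture may still have a week-8 dose. This stands, and the range above shows how much it matters.
- That leaving the clinic reflects relapse or a failed taper is plausible, but neither document says so.

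**Conclusion.** The concern holds as a gap in the sensitivity plan, chiefly for dose reduction. MAR-based imputation is a reasonable primary approach. The weakness is that the only planned check cannot respond to what happened to the dropouts.

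At the planned rates, the dose result survives equal non-response in both arms (P=0.005). It is lost if about 8 acupuncture dropouts per 50 fail while sham dropouts follow their observed rate (P=0.0275). These figures rest on the assumed number missing, the assumed scenarios and a chi-square in place of the planned mixed model, so they show possible size and are not predictions.

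Three stronger conclusions are tempting and should not be drawn. One is that the plan fails to test MAR: the assumption can only be stressed, not tested. Another is that both primary results are equally exposed: craving would need a shift of about 40 mm under the planning assumptions. The third is that a positive dose result would be an artefact of imputation: nothing in the documents shows that. The point merits a change to the SAP but does not invalidate the primary analysis.

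**What to change.** In SAP 7.5, pre-specify the following on the FAS, so that only the missing-data assumption changes:

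1. For dose reduction, count a missing week-8 dose as non-response in both arms.
2. For dose reduction, run a delta-adjusted tipping-point analysis that penalises imputed acupuncture values only, in steps until P exceeds 0.025. Item 1 treats the arms alike and would miss the asymmetric case. State whether the shift is applied to the imputed dose or to responder status.
3. For craving, run the same one-sided tipping-point analysis and report the shift reached.

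Analyse the imputed data sets separately and pool by Rubin's rules. The current SAP 7.2 step, "By calculating the median of all estimated values for missing data, the 100 imputed datasets are merged into one", discards between-imputation variance, so tipping points built on it would look more secure than they are.

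Optionally repeat item 1 on all randomised patients, because the SAP's FAS leaves out those with no session or no efficacy measure. Keep per-protocol as supportive.

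The cost is a little programming and one more set of results that may look less favourable. Trial conduct and sample size do not change. For craving, the tipping point may well help the sponsor by showing how robust the result is.

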### **7.6 Safety Analyses**

All adverse events and serious adverse events will be listed. Adverse events include the acupuncture-related adverse events and other adverse events. Chi-square test or Fisher's exact test will be used to compare the incidence of adverse events between the manual acupuncture and sham control groups.

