## **2. Study Objectives and Hypothesis**

The aim of this study is to evaluate the efficacy and safety of manual acupuncture intervention for MMT clients through a multicenter clinical randomized controlled trial, comparing it with non-penetrating sham acupuncture.

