## **3. Design**

### **3.1 Overview**

This parallel-arm, patient-blinded, multicenter, randomized, controlled trial will be performed to demonstrate the safety and effectiveness of manual acupuncture intervention for MMT clients.

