## **6. Statistical Considerations**

### **6.1 Study Hypothesis**

The primary study hypothesis is that manual acupuncture is more efficacy than sham acupuncture in reducing methadone dose and opioids craving in MMT clients.

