### **7.4 Analyses for Outcomes**

The analysis of proportion of participants with at least 20% reduction from baseline in the amount of methadone dose is performed using a generalized linear mixed model. For opioid craving VAS and all secondary outcomes, analysis is conducted utilizing a

linear mixed-model. For above models, values measured at baseline are used as covariates; intervention assignment, visit and intervention  $\times$  visit interaction are as fixed effects; and treatment centre and centre  $\times$  intervention interaction are as random effects. Before building the final model, we assess the poolability of treatment effects across centres by including centre  $\times$  intervention interaction in the model. If *P*-values corresponding to the interaction term for both primary endpoints are greater than 0.10, the treatment effect is homogenous across centres and centre  $\times$  intervention interaction will not be included in the final model. Primary outcomes use 2-sided tests at the 2.5% significance level. All other statistical tests are 2-sided at the 5% significance level. Dynamic data on the reduction in the methadone consumption and the opioid craving VAS score will be demonstrated in the figures, separated by two groups. Each row in the figures represents the reduction dose of the daily consumption of methadone (the opioid craving VAS score) for one participant. To investigate the relationship between daily consumption of methadone and the intensity of opioid craving over a 20-week period, scatter plots will be employed as a visual representation in this study with the x-axis representing the opioid craving VAS and the y-axis representing the methadone dose. The resulting scatter plot allows for the examination of the correlation between these two variables, providing insights into the potential influence of methadone intake on opioid craving levels over time.

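### SAP 3.1 promises to demonstrate safety, but the only planned between-arm safety result is a significance test on about 50 per arm, and non-significance there cannot demonstrate safety

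*Combined protocol and SAP*

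**What the plan says.** The SAP describes the safety aim in two ways. SAP 3.1 (Overview) says the trial "will be performed to demonstrate the safety and effectiveness of manual acupuncture intervention for MMT clients". SAP 2 (Study Objectives and Hypothesis), like protocol 2.2, is more modest: "The aim of this study is to evaluate the efficacy and safety of manual acupuncture intervention for MMT clients". The formal hypothesis in SAP 6.1 concerns efficacy only: "The primary study hypothesis is that manual acupuncture is more efficacy than sham acupuncture in reducing methadone dose and opioids craving in MMT clients".

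SAP 7.6 (Safety Analyses) lists adverse events and serious adverse events and then plans one comparison: a chi-square or Fisher's exact test "will be used to compare the incidence of adverse events between the manual acupuncture and sham control groups". The level comes from SAP 7.4: "All other statistical tests are 2-sided at the 5% significance level". No confidence interval, margin, expected event rate or safety power is given.

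The sample size in protocol section 10 rests on the dose-reduction rate and craving: "42 participants per group are needed at 5% significance with 90% power", raised for attrition so that "at least 50 participants per group (n = 100 in total) are required".

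The two definitions of an adverse event differ. Protocol section 8 confines the term to events associated with acupuncture. SAP 7.6 also counts other adverse events.

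**The concern.** A test of no difference can give evidence that the arms differ. Failing to reject gives no evidence that they are alike unless an interval shows which excesses the data exclude. The plan promises a demonstration of safety, and its only inferential tool is such a test, in a sample sized for a 34-point efficacy difference (70% versus 36%).

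The comparator is a non-penetrating sham, and the events named in protocol section 8 include hematoma, infection and bleeding, so an excess with real needling is plausible. If the report shows only incidences and a P-value above 0.05, readers could take that as comparable safety while a clinically relevant excess remains compatible with the data.

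**Working it through.** **1. The plan's own figure.** Inputs from protocol section 10: 70% versus 36%, two-sided 5%, 90% power, 15% attrition. With mean rate 0.53:

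- pooled-variance formula: n = [1.960·√(2·0.53·0.47) + 1.282·√(0.70·0.30 + 0.36·0.64)]² / 0.34² = 43.2, so 44 per arm;
- unpooled formula: n = (1.960 + 1.282)²·(0.2100 + 0.2304) / 0.34² = 40.0, so 41 per arm.

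The stated 42 lies between them, and 42/0.85 = 49.4, so 50. The figure is reproduced. No adverse event rate enters it. Protocol section 11 defines the safety population as everyone randomized and treated at least once, so about 50 per arm is the right number for safety.

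**2. Chance of missing an excess.** Let X and Y be independent binomial counts of participants with an event, n = 50 each, with rates p₀ (sham) and p₁ (acupuncture). The miss rate is 1 − Σ Pr(X = x)·Pr(Y = y), summed over all pairs (x, y) with test P ≤ 0.05, by full enumeration. **All rates are assumptions.** SAP 7.6 does not say when each test applies, so the last column assumes the usual rule: Fisher if any expected count is below 5, otherwise uncorrected chi-square.

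| Sham vs acupuncture | Ratio | Missed, Fisher | Missed, chi-square or Fisher |
|---|---|---|---|
| 2% vs 4% | 2 | 99% | 99% |
| 5% vs 10% | 2 | 94% | 91% |
| 2% vs 10% | 5 | 81% | 79% |
| 10% vs 20% | 2 | 81% | 70% |
| 5% vs 15% | 3 | 76% | 65% |
| 10% vs 25% | 2.5 | 59% | 47% |
| 5% vs 20% | 4 | 49% | 36% |
| 20% vs 40% | 2 | 48% | 40% |
| 10% vs 30% | 3 | 36% | 27% |
| 5% vs 25% | 5 | 25% | 15% |
| 10% vs 50% | 5 | under 1% | under 1% |

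Fisher's test reaches 80% power only at about 2% vs 21%, 5% vs 26.5% or 10% vs 34.5%.

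**3. Illustrative counts, with no assumed rate.** Take 1/50 sham and 5/50 acupuncture. Each expected count of events is 3, so Fisher applies:

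- P = 2·[C(50,6) + 50·C(50,5)] / C(100,6) = 2·(0.0133 + 0.0889) = 0.20.
- Wilson 95% limits: 0.0435 to 0.2136 for 5/50, and 0.0035 to 0.1050 for 1/50. The difference is 0.08.
- Newcombe lower limit: 0.08 − √[(0.10 − 0.0435)² + (0.1050 − 0.02)²] = −0.022.
- Newcombe upper limit: 0.08 + √[(0.2136 − 0.10)² + (0.02 − 0.0035)²] = +0.195.

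The P-value is unremarkable, but an excess of nearly 20 points is not excluded.

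Two further cases:

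- 0/50 vs 5/50 is still non-significant by Fisher: P = 2·C(50,5)/C(100,5) = 0.056.
- Identical counts of 5/50 give a Newcombe interval of −12.7 to +12.7 points. Even a perfect tie therefore excludes only an excess above about 13 points.

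**The case against.** Four arguments on the other side deserve weight.

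*The objective is to evaluate, not to demonstrate.* This is largely right. Protocol 2.2 and SAP 2 both say evaluate, and the stronger verb for safety stands only in the SAP 3.1 overview. Listing and comparing events is a form of evaluation. What remains is that the SAP contradicts itself on how strong a claim it seeks, and no planned analysis supports the stronger one.

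*There is no decision rule.* A reader might infer that the SAP treats P > 0.05 as proof of safety, or that the test is a pass/fail criterion. The documents do not say so: SAP 7.6 plans a comparison and sets no rule for reading it. The narrower point stands, because no other between-arm safety result is planned.

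*The miss rates depend on the chosen rates.* This is correct. A reader might take a few pairs from the table and conclude that two- to five-fold excesses are generally missed 60% to 80% of the time. That does not hold, since the same range of ratios gives anything from about 99% to under 1%, depending on the sham rate. That rate in turn depends on which adverse event definition applies.

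*Sizing on efficacy is ordinary, and other safety data exist.* Both statements are true. Protocol section 8 also collects laboratory tests and an electrocardiogram at screening and after 8 weeks, and requires serious events to be reported within 24 hours. SAP 7.6 gives no between-arm analysis of the laboratory or ECG data, however, so they do not fill the gap. Nobody need enlarge the trial for safety. The issue is how a small comparison is reported.

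**Conclusion.** The point holds in a limited form and is worth acting on. As planned, the safety comparison can reveal a large excess of adverse events but cannot support a statement that safety has been demonstrated, whatever the P-value.

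Under assumed sham rates of 2% to 10%, excesses of 8 to 10 percentage points are missed by Fisher's test in about three quarters to four fifths of trials. Larger excesses on higher base rates would usually be found. The conclusion that non-significance cannot demonstrate safety needs no assumed rate: it follows from the missing interval and margin and from the interval widths at 50 per arm. The primary efficacy analyses are not affected.

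**What to change.** 1. **SAP 7.6.** Make the between-arm safety result the risk difference (acupuncture minus sham) in participants with at least one adverse event, with a two-sided 95% confidence interval by Newcombe's method or an exact method, named in advance. State the largest excess that the upper limit excludes. Keep the chi-square or Fisher P-value as descriptive, and add that P > 0.05 will not be reported as no difference. Say that the interval governs, because the two can disagree: 1/50 vs 7/50 gives Fisher P = 0.059 with a Newcombe interval of about +1 to +24 points.
2. **SAP 3.1.** For safety, replace the verb demonstrate with evaluate, to match protocol 2.2 and SAP 2.
3. **Protocol section 8 and SAP 7.6.** Reconcile the two adverse event definitions before unblinding, since the definition determines the incidence being compared.

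The cost is some SAP wording and one extra estimate from counts already collected, with no new data and no change in sample size. The drawback for the sponsor is a less favourable safety statement, since even equal counts of 5/50 would leave an excess of up to about 13 points open.

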## 5.2 Sham Control Group

Non-penetrating sham acupuncture will be applied at the same acupoints as the

manual acupuncture group. Sterile stainless-steel disposable blunt acupuncture needles (Huatuo, Suzhou, China; lengths and diameters: 25 mm × 0.3 mm) are used as sham needles. When they are fixed on the skin through acupuncture auxiliary device, patients felt a pricking sensation, simulating a puncture of the skin. However, the needles do not penetrate the skin when they are pressed by acupuncturists.

Patient-blinded acupuncture intervention uses a special acupuncture auxiliary device (**Figure 3**). The device has already been granted a patent by China's national intellectual property administration (No. ZL 202223328917.3). The device consists of a plastic pedestal and a guide tube, and the shape of the device used is the same in both groups. For real acupuncture, we use hollow instruments where needles can be inserted hygienically directly into the skin. For placebo acupuncture, we use non-hollow instruments and blunt needles. To achieve a single-blind outcome, the acupuncturist fixes an acupuncture auxiliary and a needle or placebo needle to the skin of the acupoint after sterilization. Then the acupuncturist quickly taps the top of the tube to make the needle go downward and removes the tube. Therefore, participants are blinded to group and intervention by entering the needle through this acupuncture auxiliary device.

[figure not shown]

Figure 3 acupuncture auxiliary device (A: hollow instruments for real acupuncture. B: non-hollow instruments for placebo acupuncture)

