## **8. Safety**

All participants will have some tests to check up on their bodies at screening and after 8-week intervention. Those tests are relative to the heart, liver, kidney, and other organs, including white blood cell count, hematocrit, hemoglobin, platelet, aspartate aminotransferase/alanine aminotransferase, blood urea nitrogen, creatinine, gamma-glutamyl transpeptidase, erythrocyte sedimentation rate and electrocardiogram.

Adverse events (AEs) are defined as events associated with acupuncture including fainting, hematoma, broken needle, infection, and bleeding. If any adverse events occur, these will be recorded by the acupuncturist and the treatment will be temporarily stopped. Every AEs will be fully recorded on the case report forms (CRFs) including all details of AEs. Serious AEs that threaten to participant's life or result in hospitalization will be reported to the Research Ethics Committee concerned within 24 hours.

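### SAP 7.6 names two classes of adverse event but only one between-arm comparison, so against a non-penetrating sham the test cannot show whether harms other than needle events differ

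*Combined protocol and SAP*

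**What the plan says.** SAP 7.6 (Safety Analyses) has three elements. It promises a listing: "All adverse events and serious adverse events will be listed". It sets the scope: "Adverse events include the acupuncture-related adverse events and other adverse events". It then names one comparison, a chi-square or Fisher test to "compare the incidence of adverse events between the manual acupuncture and sham control groups". No table, estimate or test by class is specified. SAP 7.4 puts every test other than those of the primary outcomes at two-sided 5%.

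Three other places bear on this:

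- **Protocol section 5.2** describes the comparator: "the needles do not penetrate the skin when they are pressed by acupuncturists".
- **Protocol section 8** defines the term more narrowly than the SAP: "Adverse events (AEs) are defined as events associated with acupuncture including fainting, hematoma, broken needle, infection, and bleeding". When events occur, "these will be recorded by the acupuncturist and the treatment will be temporarily stopped". Under protocol section 3.2 the acupuncturist is not blinded.
- **Protocol section 11** defines the safety population as everyone randomised and treated at least once. SAP 6.2 defines only the full analysis and per-protocol sets.

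**The concern.** Four of the five events named in protocol section 8 (hematoma, broken needle, infection, bleeding) arise chiefly from puncturing the skin. Fainting does not. Active-arm participants have 24 sessions at 10 points each (4 Sishen, 3 Dingshen and 3 Shouzhi on one hand), or 24 × 10 = 240 insertions. Sham participants should have none. A difference in needle events is therefore expected from the design and says nothing about other harms.

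If both classes go into one incidence, one P-value has to serve two questions: how much harm the needling itself does, and whether other harms differ between arms. A significant result could come from bruises alone. A non-significant one could be two opposite differences offsetting each other. Safety is part of the stated aim (protocol 2.2, SAP 2), and this is the only between-arm comparison of adverse events in the plan.

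**Working it through.** **Arm size.** The plan gives no figure for the adverse-event comparison, so only the arm size can be checked. Protocol section 10 states 42 per group (70% vs 36%, 5% significance, 90% power) and 50 after 15% attrition.

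- Unpooled variance: (1.960 + 1.282)² × (0.70×0.30 + 0.36×0.64) / 0.34² = 10.51 × 0.4404 / 0.1156 = 40.0, i.e. 41 per group.
- Pooled variance gives 44, so the stated 42 lies between the two.
- 42 / 0.85 = 49.4, i.e. 50. I use 50 per arm.

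**Assumptions.** All event rates below are assumed. Needle events occur at rate *a* on acupuncture and 0 on sham. Other events occur at rates *b* (acupuncture) and *c* (sham), independently of needle events. The incidence of any event is then 1 − (1 − *a*)(1 − *b*) on acupuncture and *c* on sham. The probability of two-sided P < 0.05 comes from exact enumeration of two binomials with n = 50, by Fisher's exact test and by uncorrected chi-square.

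**Case 1: other harms equal (*b* = *c*).** Example: *a* = 20%, *b* = 10% gives 1 − 0.80 × 0.90 = 28% versus 10%.

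| Needle events, *a* vs 0 | Other events, each arm | Any event | P < 0.05, Fisher | P < 0.05, chi-square |
|---|---|---|---|---|
| 10% | 10% | 19% vs 10% | 16% | 26% |
| 10% | 20% | 28% vs 20% | 11% | 16% |
| 15% | 10% | 23.5% vs 10% | 34% | 46% |
| 15% | 20% | 32% vs 20% | 21% | 28% |
| 20% | 10% | 28% vs 10% | 55% | 66% |
| 20% | 20% | 36% vs 20% | 35% | 43% |

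If no other events occurred at all, 6 versus 0 participants would already be significant (Fisher P = 0.027). If the sham also produced needle-type events in 2% of participants, the 20%-needle rows would fall to 44% and 29% (Fisher).

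**Case 2: other harms more frequent on sham (*b* = 10%, *c* = 30%).** Tested separately, the difference is detected in 64% of trials (Fisher; chi-square 73%). Pooled:

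- *a* = 10%: 19% vs 30%, significant in 19% (chi-square 25%).
- *a* = 15%: 23.5% vs 30%, significant in 8% (11%).
- *a* = 20%: 28% vs 30%, significant in 3.5% (5.6%).

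**Case 3: other harms more frequent on acupuncture (*b* = 30%, *c* = 10%).** The separate test again detects this in 64% (Fisher). The pooled test is significant in 87% at *a* = 10% and 97% at *a* = 20%. Nothing is masked numerically, but the result does not say which class caused it.

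**The case against.** The case for leaving SAP 7.6 alone has several parts.

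- **Pooling is inferred.** The section does not say that the two classes are combined. This stands as a caution. Still, the sentence before the test defines the term as both classes, and no other comparison is named.
- **Everything is listed.** A result driven by bruises would be visible. That is so, and the problem is one of interpretation, not of an invalid test. A listing, however, gives no between-arm estimate.
- **Tapering harms are analysed elsewhere.** This stands in large part. COWS is measured at seven post-baseline visits, SAP 5.2 lists the urine test as a secondary outcome, and SAP 7.4 covers all secondary outcomes. A reader might infer that the pooled test is the only safeguard against withdrawal or relapse going unnoticed. The documents do not support that. What lacks its own comparison is mainly serious events, hospitalisation and other clinical events.
- **Needle harms are real harms.** This stands. A reader might conclude that the safety verdict should rest on non-needle events only. That would remove the intervention's own injuries from its safety assessment. Nor are acupuncture-related and needle-site the same class, since protocol section 8 includes fainting.
- **Under protocol section 8 there may be nothing to pool.** If only acupuncture-associated events are recorded, the test is close to puncture versus no puncture. This does not rescue the plan, because other harms would then not be compared at all. It does mean that the definition has to be settled first.

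**Conclusion.** The point holds as one of interpretation. With a single incidence and a sham that does not break the skin, a significant result may come from needle events alone, and no result can show whether other harms differ.

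The size depends on rates the documents do not give. Over the range assumed here, with other harms equal, the pooled test is significant in about 11–55% of trials (Fisher; 16–66% chi-square). The lower end applies when needle events are around 10%, so it cannot be said that the test would usually raise a false alarm.

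A reader might also infer that pooling can hide an excess of other harms on acupuncture. It does not do so numerically, because needle events add to such an excess and make significance more likely; only the attribution is lost. Numerical masking needs other harms to be more frequent on sham. That is plausible if acupuncture eases tapering, and what would be hidden is then a benefit.

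The primary analyses are untouched. This is a worthwhile clarification of modest priority.

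**What to change.** 1. **Reconcile the definitions first.** Protocol section 8 (acupuncture-associated events only) and SAP 7.6 (acupuncture-related and other events) must agree, so that other events are collected in both arms.
2. **Report by class.** In SAP 7.6, count participants with at least one event by arm, separately for acupuncture-related events, other adverse events and serious adverse events. Give n, %, risk difference and 95% CI for each, and keep overall incidence as a further row. Use the safety population of protocol section 11 and add it to SAP 6.2.
3. **State the basis of the conclusion.** Draw the safety conclusion from both classes, not from the pooled P-value.
4. **Fix the classes in advance.** Assign them by listed event type, so that the split does not depend on case-by-case attribution by the unblinded acupuncturist who records the events.

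The analysis costs SAP wording and one table, with no added participants or visits. Reconciling the definition may also mean changing the protocol text and the event collection. The statistical downside is fewer events per class and so wider intervals. Some dependence on attribution remains for events that do not fit the listed types.
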